## Methods

### Design

A nonrandomized pilot study design will be used with all participants receiving 16 weekly sessions of e-CBT. Functional magnetic resonance imaging (fMRI) will be conducted at baseline and posttreatment to evaluate activation level changes in the basal ganglia and frontal cortex. Clinically validated symptomology questionnaires will be used to evaluate treatment efficacy. In addition, qualitative interviews will be conducted to gather personal demographic information as well as information regarding participant experience while using the web-based psychotherapy clinic. The pilot study has been registered on the ClinicalTrials.gov Protocol Registration and Results System (NCT04630197). In addition, ethics approval has been obtained from the Queen’s University Health Sciences and Affiliated Teaching Hospitals Research Ethics Board (HSREB; file number 6031276).

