### Participants

Participants (n=10) will be recruited from family medicine and psychiatric clinics at Queen’s University and Kingston Health Sciences Centre sites (Hotel Dieu Hospital and Kingston General Hospital) in Kingston, Ontario, Canada. In addition, local and social media advertisements will be used. Participants will be enrolled in the study based on referrals from outpatient clinics and family doctors as well as self-referrals. Those invited and interested in participating will have the study protocol explained and an evaluation done by a psychiatrist on the research team through a secured video appointment. Participants will be evaluated for a diagnosis of OCD based on the *Diagnostic and Statistical Manual of Mental Disorders, 5th Edition* [44]. After a diagnosis of OCD is confirmed and the participant is given written and verbal instructions on how to participate in the study, informed consent will be obtained.

The inclusion criteria include the following: between the ages of 18 and 65 years at the start of the study, a diagnosis of OCD according to the *Diagnostic and Statistical Manual of Mental Disorders, 5th Edition* criteria, competence to consent to participate, ability to speak and read English, and consistent and reliable access to the internet. Exclusion criteria include the following: having any metal implants or additional factors deemed not safe for an MRI scan, active psychosis, acute mania, severe alcohol or substance use disorder, and/or active suicidal or homicidal ideation. In addition, if a participant is currently receiving another form of psychotherapy, they will be excluded from the study.

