### Outcomes

The primary outcome measure will be changes in activation levels of the basal ganglia and frontal cortex. This will be collected through detectable changes in BOLD values from the fMRI scans at baseline and after treatment (week 16). The secondary outcomes will be changes in symptom severity, quality of life, and functioning. Changes in symptom severity will be evaluated using clinical symptomatology questionnaires (Yale-Brown Obsessive-Compulsive Scale and Obsessive-Compulsive Inventory, Revised) [46,47]. Changes in quality of life will be measured using the Quality of Life and Enjoyment Questionnaire [48]. Changes in levels of functioning will be measured using the Sheehan Disability Scale [49]. All questionnaires will be collected directly through OPTT at baseline, after session 8, and after treatment (week 16).

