### Compliance

As with all mental health disorders, treatment compliance is always an area of focus when designing interventions. Participants will have the importance of treatment compliance explained to them during the informed consent process, and participants will need to submit their homework assignments through OPTT before gaining access to their next treatment session. From a previous meta-analysis conducted, the estimated completion rate from in-person psychotherapy is approximately 75% [50]. Additional meta-analyses found treatment adherence for web-based psychotherapy to be between 61% and 66%, with no significant difference with in-person psychotherapy [51-53]. A study investigating the efficacy of a 10-session e-CBT program for OCD had a mean completion of 7.28 sessions [54]. Previous research using OPTT indicated participants completed >8 sessions on average, with over half the participants completing all sessions. In a previous project using e-CBT for patients with generalized anxiety disorder, 90% of participants completed 10-12 weeks of the 12-week program, with over 75% of participants being retained for a 12-month follow-up [55].

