### Analysis

For the fMRI data (primary outcome), a 0.5% (eff=0.005) change in BOLD hemodynamic response function will be considered a detectable signal variation between conditions (*P*>10^-6^). An estimated paradigm of expected BOLD response will be created, and the correlation between the real and expected signals will be calculated to detect noise using a general linear model:

S = βX + e **(1)**

Where, S is the time-series data, β is the value for each pattern, X is the set of time-series patterns, and e is the residual.

The general linear model will provide a β value for each term in the basis set and a T value for each β. The BOLD contrast between conditions and scanning periods (ie, baseline and posttreatment) will be evaluated using one- and two-sample *t* tests, assuming a normal distribution. Realignment parameter regressors for the testing conditions will be implemented [56,57]. The effects at each condition will enter a group analysis using a random-effects model [58]. A group-level comparison will be used with small volume corrections performed for multiple comparisons using the Gaussian random field theory. Missing data points can be accounted for in the analysis with usable questionnaires and fMRI data using the linear model.

For questionnaire scores (secondary outcomes), a linear regression analysis will be used to identify variables associated with the outcome measures while controlling for demographic variables (ie, age, sex, and gender). Repeated measures of analysis of variance will be conducted to determine changes between periods (ie, baseline, week 8, and posttreatment) questionnaire scores. Greenhouse-Geisser adjustment for F-statistics and Bonferroni corrections for multiple comparisons will be used. Using the Pearson correlation coefficient, the correlation between the questionnaire score and the BOLD response will be evaluated. Data outliers will be defined as SD 3.29 away from the mean on scores.

Skew and kurtosis will be analyzed assuming a normal distribution in the questionnaire and fMRI data at all collection time points. Age, gender, and sex variables will be considered in knowledge creation and translation.

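### With 10 participants, and the mean and SD taken at each visit, the 3.29-SD outlier rule for questionnaire scores can never flag a value

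*Protocol article*

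**What the plan says.** The questionnaire paragraph of the Analysis section gives one explicit outlier criterion: "Data outliers will be defined as SD 3.29 away from the mean on scores". It does not say whether the mean and SD are computed per time point, over all time points together, or taken from an external source. It also does not say what happens to a flagged value.

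The sample is fixed under Participants: "Participants (n=10) will be recruited from family medicine and psychiatric clinics". The Design section shows that no comparison group adds scores to these 10: "A nonrandomized pilot study design will be used with all participants receiving 16 weekly sessions of e-CBT". Under Outcomes, the questionnaires are collected three times (baseline, after session 8, week 16) directly through the online therapy platform.

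The Analysis section adds one other distributional check: "Skew and kurtosis will be analyzed assuming a normal distribution in the questionnaire and fMRI data at all collection time points". It attaches no cut-off and no consequence to it. The methods planned for the questionnaire scores are linear regression adjusting for demographic variables, repeated-measures ANOVA, and a Pearson correlation with the BOLD response.

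**The concern.** The cut-off 3.29 matches the two-sided 0.001 point of the normal distribution (3.2905). A cut-off of that kind is useful in samples large enough for a value to get that far from a mean and SD to which it contributes itself. In a very small sample an extreme value inflates the SD by which it is judged, and there is a hard ceiling on its standardized distance. If that ceiling lies below 3.29 at n=10, the prespecified rule has only one possible result: no outliers.

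That matters because least-squares methods on 10 people can be driven by one person. The questionnaire-BOLD correlation is the most exposed, and it answers the second study question listed under Objectives. A report could truthfully say that no score met the prespecified outlier definition while a single participant produced the association.

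**Working it through.** **Inputs from the protocol article.** Cut-off 3.29 SD (Analysis); n=10 (Participants); one group (Design); three questionnaire time points (Outcomes). The article gives no derivation of the cut-off, so there is no figure of the plan's own to reproduce.

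**1. The ceiling.** Let d be the deviation of one value from the sample mean. The other n-1 deviations sum to -d, so their sum of squares is at least d²/(n-1). The total sum of squares is then at least d² + d²/(n-1) = d²·n/(n-1). Dividing by n-1 gives s² ≥ d²·n/(n-1)², hence

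|d|/s ≤ (n-1)/√n with the usual n-1 SD, or √(n-1) with the n-divisor SD.

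This is algebra and holds for any distribution.

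**2. Numbers put in.**

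| n | (n-1)/√n | √(n-1) | Can 3.29 be exceeded? |
|---|---|---|---|
| 6 | 2.041 | 2.236 | no |
| 7 | 2.268 | 2.449 | no |
| 8 | 2.475 | 2.646 | no |
| 10 | 2.846 | 3.000 | no |
| 12 | 3.175 | 3.317 | only with n-divisor SD |
| 13 | 3.328 | 3.464 | yes |

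Nine equal values and one enormous value reach exactly 2.846 and 3.000. In 2 million simulated samples of size 10 from a Cauchy distribution, which is very heavy-tailed, the largest value of |d|/s was also 2.846. Change scores from the same 10 people obey the same ceiling.

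The rows below 10 show the effect of missing visits. The Compliance section cites adherence of 61% to 66% for web-based psychotherapy. If adherence meant questionnaire completion, which is an assumption, 6 or 7 of 10 would remain at the end.

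**3. Alternative reading: scores pooled over visits.** With 30 scores per scale, one extreme score can reach 29/√30 = 5.295 and two equal extremes 3.679, so the rule could fire. One participant equally extreme at all three visits would reach only 2.950 and would still pass.

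**4. What an unflagged point can do to the correlation.** Take nine participants with mean 0, SD 1 and zero correlation, and a tenth at (5, 5), that is, 5 of those SDs out on both axes.

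- Sum of squares on each axis: 8 + (9/10)·25 = 30.5
- Sum of cross-products: 0 + (9/10)·25 = 22.5
- r = 22.5/30.5 = 0.738
- t = 0.738·√(8/(1-0.738²)) = 3.09 on 8 df, P = 0.015
- Standardized distance of the tenth point: (5-0.5)/√(30.5/9) = 2.44

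The point creates a nominally significant correlation and stays well under 3.29. The size of 5 SD is an illustration. The article gives no score distribution from which to judge how likely it is.

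**The case against.** **The per-visit reading is not written down.** This stands as a condition on the finding. Pooled over visits, or against an external mean and SD, the rule could fire. But no pooling and no reference values are stated, and the next distributional check in the same section is made at every collection time point. Pooling would also mix treatment change into the SD.

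**Skew and kurtosis are checked as well.** This stands in part. A gross error would distort the skew visibly, so a reader who infers that the plan has no way at all of noticing an aberrant value goes too far. The check nevertheless identifies no individual score, has no threshold and leads to no action.

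**The primary outcome is not affected.** Correct. A reader might infer that the BOLD t tests are also left unprotected by this rule. The documents do not support that: the rule is worded for scores and sits in the questionnaire paragraph, apart from the fMRI contrasts.

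**Gross data-entry errors are unlikely.** Also fair. It is tempting to illustrate the problem with a mistyped score, but the questionnaires are collected directly on the platform and no manual transcription is described. Whether the platform restricts values is not stated. The correlation example needs no such error.

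**The practical effect is small.** An idle rule leaves all data in the analysis, and the remedy also keeps genuine values in the main analysis. What is lost is the warning and the accompanying sensitivity result, not the main estimate.

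**Conclusion.** The point holds, with a condition. With 10 participants and the mean and SD taken from the scores at each time point, the largest attainable distance is 2.85 sample SDs (3.00 with the n-divisor SD), so the 3.29 rule cannot identify any score. It becomes possible only at n=13 (n=12 with the n-divisor SD), and missing visits lower the ceiling, to 2.27 at 7 completers.

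The consequence is limited to the regression and repeated-measures ANOVA of the questionnaire scores and to their Pearson correlation with BOLD. The correlation is the most exposed: one unflagged point at z=2.44 can yield r=0.74, P=0.015. The conclusion assumes the per-visit reading, which the text suggests but does not state. It does not show that such a point will occur, and it does not reach the primary fMRI comparison. This is a stated rule that fails at the trial's own sample size. It should be corrected, at modest consequence if it is not.

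**What to change.** Replace the 3.29-SD sentence with a rule that can operate at n=10 and say what it triggers. One workable form:

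- At each time point, check every score against the permitted range of its scale.
- At each time point, flag scores with |x - median|/(1.4826 × MAD) > 3.5, where MAD is the median absolute deviation from the median.
- Keep genuine values in the main analysis.
- Report the questionnaire results and the questionnaire-BOLD correlation with and without flagged values, with Spearman beside Pearson.

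The MAD cut-off is one reasonable choice among several; what matters is that the rule can fire and that its consequence is fixed in advance.

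The cost is a short replacement text and a few extra analysis lines, with no added burden on participants. The downside is false flags: in simulation, about 13% of clean normal samples of 10 had at least one value flagged, and this applies to each scale at each visit. A flag should therefore lead to a sensitivity analysis only, never to automatic deletion.

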### Ethics and Privacy

The pilot study has received approval from the Queen’s University HSREB. Only the care providers involved in the care of the participants will have access to their information. Participants will only be identifiable by an identification number on the OPTT platform, and hard copies of consent forms with participant identity will be stored securely on site and will be destroyed 5 years after study completion. Only anonymized data will be provided to the analysis team members. OPTT is compliant with the Health Insurance Portability and Accountability Act, Personal Information Protection and Electronic Documents Act, and Service Organization Control–2. In addition, all servers and databases will be hosted in the Amazon Web Service Canada cloud infrastructure, which is managed by Medstack to assure all provincial and federal privacy and security regulations are met. OPTT will only collect anonymized metadata to improve its service quality and provide advanced analytics to the research team. OPTT will encrypt all data, and no employee will have direct access to patient data. All encrypted backups will be kept in the S3 storage dedicated to Queen’s University.

## Results

The pilot study is currently being conducted at Queen’s University by the members of the research team. This pilot study is a nonrandomized, open-label study, with a plan for an expanded randomized controlled trial in the future. The pilot study received ethics approval from the Queen’s University HSREB in December 2020, and the recruitment of participants began in January 2021. To date, 5 participants have been seen for initial assessments and enrolled in the study. Data collection is anticipated to begin in June 2021, with collection and analyses concluding by January and February 2022, respectively. All reporting of this study has been and will be in accordance with the GUIDance for the rEporting of intervention Development (GUIDED) and Template for Intervention Description and Replication (TIDieR) reporting checklists and guides (Multimedia Appendices 1 and 2).

## Discussion

This trial can contribute to creating more effective treatments for OCD in the future. However, to do this, we must understand the pathophysiology and etiology of this debilitating and prevalent condition. Currently, there is no conclusive information on the pathophysiology and etiology of OCD. Although CBT with ERP is currently the frontline psychotherapy for OCD, the efficacy of this treatment, along with those of new and innovative ones, can be improved drastically if we understand better how treatment affects neural anxiety processing and cognitive functioning. By measuring brain activation levels during exposure to neutral and anxiety-inducing stimuli pre- and posttreatment, we can observe how the suspected regions involved in OCD pathology (basal ganglia and frontal cortex) change following treatment. This can enlighten us on various aspects of OCD, including whether effective treatment results in changes to activation levels, whether symptom improvement is correlated to changes in activation levels, and if there are any identifiers for brain activation levels for responders and nonresponders to treatment. If how patients with OCD process anxiety-inducing stimuli (ie, dirty dishes if cleanliness is a patient's obsession) can be understood better, more targeted treatments can be given to specifically alter these parts of a person’s cognition.

## Appendix

Multimedia Appendix 1 GUIDED (Guidance for the Reporting of Intervention Development) report checklist.

Multimedia Appendix 2 TIDieR (Template for Intervention Description and Replication) report checklist.

## Abbreviations

BOLD: blood oxygen level–dependent
CBT: cognitive behavioral therapy
e-CBT: electronically delivered cognitive behavioral therapy
ERP: exposure and response prevention
fMRI: functional magnetic resonance imaging
FOV: field of view
GE-EPI: gradient-echo echo-planar imaging
GUIDED: GUIDance for the rEporting of intervention Development
HSREB: Health Sciences and Affiliated Teaching Hospitals Research Ethics Board
MPRAGE: magnetization-prepared rapid acquisition gradient-echo
OCD: obsessive-compulsive disorder
OPTT: Online Psychotherapy Tool
TE: echo time
TIDieR: Template for Intervention Description and Replication
TR: repetition time
